### Data collection

Data are collected at baseline, before randomisation, and at follow-up assessments 2, 12, 26, and 52 weeks after treatment. The questionnaires are preferably filled out online, although a paper version is also available. All paper questionnaires are scanned and stored on a secure disk. The online questionnaires are saved by the online questionnaire program, and a backup is made regularly.

Photographs are taken at all visits. Volume of the keloid is measured at baseline and after the skin has completely healed at 12, 26, and 52 weeks after treatment.

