### Statistical analysis

Baseline demographic and clinical characteristics will be presented as proportions or means and standard deviations (SD) where appropriate. Because of the longitudinal data with multiple influencing factors, a sophisticated model is necessary. Mixed models (also called multilevel linear regression analysis) is a technique that efficiently uses longitudinal data and can work with patients’ data even though measures at certain time points may be missing.

The units of analysis are the repeated measurements of the patient (first level), not the keloid, because we use several QoL measures that are not measurable for the unit keloid. The second level will be the individuals participating in the study. If necessary, a third level of subgroups with specific characteristics (skin type, duration of keloid disease and location of the keloid) can be added. If the third level is shown to improve the fit of the model, it will be incorporated in the model. We will use backward elimination and start with an unstructured covariance structure for intercept and time (slope). Simplifications of the random part of the model will be tested using the deviance statistic with restricted maximum likelihood. For the fixed part we will postulate a saturated model. We take in account time, logarithm of time and squared time, treatment condition and its interactions with time. Nonsignificant effects will be excluded using Wald tests. The fit of the final fixed model will be compared with the saturated model and will be checked using ordinary maximum likelihood. When characteristics like sex, age, skin type, duration of keloid disease and location of the keloid make a significant contribution to the model, they will be incorporated in the model [34-37]. Differences between treatment effects will be expressed in terms of effect sizes, standard errors and *P* values. Effect sizes will be calculated by dividing the estimated differences by the estimated standard deviation. An effect size of 0.20 is considered a small effect, 0.50 a medium effect and 0.80 as a large effect [38].All analyses will be performed on an intention-to-treat basis. IBM SPSS version 21.0 and SAS version 9.3 will be used to perform the analyses.

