### Sample size calculation

There are no meaningful rules of thumb to estimate the sample size needed for a mixed models analysis, because, with random and fixed effects estimations, too many factors of uncertainty are involved. Therefore, a standard sample size calculation with a correction for the design effect based on the intercorrelation was used.

These calculations were performed in SPSS version 20.0 using the mixed-model ANOVA procedure as described by Aberson [39]. Type 1 error (alpha) was set at 0.05, and power (1-beta) on 0.80.

To estimate the effect size and correlation we analysed data of a natural cohort collected by one of the authors ([name]) containing general features of keloid patients and POSAS values before and after treatment with intralesional cryotherapy. This natural cohort contains measurements at baseline, and at 12, 26, and 52 weeks after treatment. It comprised POSAS observer values from one or two observers and patient values; however, many patients lacked values for some time points (56% of follow-up complete). Only a small amount of items were missing, in total 15/3378 (0.44%) items of the POSAS data were imputed following the rules described previously.

The assumed medium-sized effect of 0.5, based on a SD of around 15 (Table 1), corresponds to 7.5 points on the POSAS scale; this is slightly more than the 6 points that is regarded as a clinically significant difference. We assumed a correlation of 0.75 between time points; this was difficult to verify in the data of the natural cohort because of many incomplete cases.

**Table 1 T1:** Descriptive statistics

	**N**	**Minimum**	**Maximum**	**Mean**	**SD**
POSAS baseline	73	30	93	60.45	12.276
POSAS 12 wk post op	44	18	85	50.65	15.474
POSAS 26 wk post op	46	17	83	49.23	15.854
POSAS 52 wk post op	33	24	81	46.18	13.959
POSAS overall	196	17	93	53.32	15.20

POSAS, Patient and Observer Scar Assessment Scale score; post op, postoperative.

wk, weeks.

The analysis, based on the observed SD and expected correlation and effect size, resulted in a group size of 33 patients, taking into account a 25% loss to follow-up and the four treatment groups; this results in a total sample of 176 subjects.

No interim analysis is planned because we do not expect any severe side-effects and, by the time a sufficient part of the participants has finished follow-up, almost all participants will have had their intervention. No rules related to stopping/withdrawal from the study have been specified.

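### The primary mixed model does not pre-specify adjustment for the pre-randomisation POSAS; the precision lost is modest for a change contrast and large only for an unadjusted visit difference

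*Protocol article*

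**What the plan says.** All of the following is in the protocol article.

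- Statistical analysis gives the starting point, "For the fixed part we will postulate a saturated model", and its content: linear, logarithmic and squared time, plus "treatment condition and its interactions with time".
- It then reduces the model: "Nonsignificant effects will be excluded using Wald tests". No term is exempted, so the treatment terms fall under the same rule.
- Covariates enter conditionally: "When characteristics like sex, age, skin type, duration of keloid disease and location of the keloid make a significant contribution to the model", they are added. Baseline POSAS is not among those named.
- The modelled responses are described only in general terms: "The units of analysis are the repeated measurements of the patient (first level), not the keloid". Whether the baseline score is one of these responses is not stated, nor is the contrast that represents the treatment effect.
- Data collection fixes the timing: "Data are collected at baseline, before randomisation", with follow-up at 2, 12, 26 and 52 weeks.
- The minimisation factors (Trial design; Randomisation) are skin type, location and duration of the keloid. Baseline POSAS is not one of them.
- Sample size calculation: "We assumed a correlation of 0.75 between time points", with an effect size of 0.5 on an SD of about 15 (7.5 points), alpha 0.05, power 0.80, 33 per group, 25% loss to follow-up and 176 patients in total.

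**The concern.** Because baseline POSAS precedes randomisation, the two arms of each part share one true baseline mean, and any observed gap is chance. A model that knows this can use baseline to sharpen the treatment comparison. The stated model is not told.

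There are two readings. If baseline is one of the modelled responses, the treatment main effect in the starting model gives each arm its own baseline mean, and the treatment effect becomes either a difference at a visit or a difference in change. If baseline is not a modelled response, it enters the stated model nowhere. Neither reading commits the trial to adjustment.

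Precision is at stake, together with how far a chance baseline gap shows up in the estimate. On the protocol's own assumed correlation, baseline would be a strong predictor of follow-up. The Discussion also accepts that the trial will be underpowered if the true effect is smaller than planned, so precision that costs nothing is worth taking.

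**Working it through.** **Inputs.** From Sample size calculation: n = 33 per group, difference 7.5, SD 15, correlation r = 0.75; Table 1 SDs of 12.276 (baseline) and 13.959 (52 weeks). Assumptions of this check: two-sided 5% (sidedness is not stated), one follow-up visit, and equal SDs unless noted. The article's smooth time terms are simplified to a comparison at a single visit.

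**Step 1: reproduce the planned size.** The variance of a change score relative to a single measurement is 2(1 − r) = 2 × 0.25 = 0.50. The standardised effect is 0.5/√0.50 = 0.707. The noncentral t calculation for 80% power gives 33 per group; 33/0.75 = 44, and 4 × 44 = 176. This matches the article. A follow-up-only comparison would need 64 per group and a baseline-adjusted one 29, so neither reproduces 33.

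**Step 2: compare the three contrasts at n = 33, r = 0.75, equal SDs.** SE = 15 × √(factor) × √(2/33).

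| Contrast | Variance factor | SE | Power |
|---|---|---|---|
| Unadjusted visit difference | 1 | 3.69 | 0.52 |
| Change from baseline | 2(1 − r) = 0.50 | 2.61 | 0.81 |
| Baseline-adjusted | 1 − r² = 0.4375 | 2.44 | 0.86 |

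A generalised least squares calculation over five visits with the same correlation between all pairs returns the same three SEs. Adjusted against change: 1 − 0.4375/0.50 = 12.5% less variance.

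**Step 3: use the Table 1 SDs.** Change variance = 12.276² + 13.959² − 2r × 12.276 × 13.959. Adjusted variance = 13.959² × (1 − r²).

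- r = 0.75: 88.5 and 85.2, a gain of about 4% (power 0.89 against 0.90).
- r = 0.6: 139.9 and 124.7, a gain of about 11%.
- r = 0.5: 174.2 and 146.1, a gain of about 16%.

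The lower values of r matter because the article says the 0.75 was difficult to verify in the cohort data.

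**Step 4: chance imbalance.** With SD 12.276 and 44 per arm, the SE of the baseline gap is 12.276 × √(2/44) = 2.62, so a gap above 3 points either way occurs in about 25% of trials, in each part. At r = 0.75 with equal SDs, a 3-point gap shifts an unadjusted visit difference by 0.75 × 3 ≈ 2.3 points and a change contrast by 0.25 × 3 = 0.75 points in the opposite direction. With the Table 1 SDs the slope is 0.75 × 13.959/12.276 = 0.853, and the shifts are about 2.6 and 0.44 points. The article's clinically important difference is 6 points.

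**Step 5: effect of the elimination rule.** If time is coded so that the treatment main effect is the baseline difference, that term is truly zero and would be retained in about 5% of trials. In an idealised simulation (33 per arm, SD 15, r = 0.75), dropping it when nonsignificant gives an estimate with SD 2.49, between full adjustment (2.44) and change (2.61).

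**The case against.** The strongest reply is that treatment, time and their interaction form a standard longitudinal model. It is valid under randomisation, and its standard error already reflects chance imbalance. If baseline is a modelled response, the interaction terms compare change from baseline, so baseline is used. The sample size rests on that contrast and reaches 80% power without any amendment. Wald elimination would usually remove a null treatment main effect and leave something close to a common-baseline model. The covariate list is illustrative, so baseline POSAS is not excluded. The detail could sit in a fuller plan.

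Much of this stands. A reader might infer that the model ignores baseline altogether, or that the trial has only 52% power. The article supports neither: the first is wrong for a change contrast, and the second belongs to a visit difference, which the planned 33 does not match. Nor is a free baseline mean certain beyond the saturated starting model, and even there it requires baseline to be a modelled response.

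The reply does not remove the point. Elimination and the open covariate list both depend on significance in the data at hand, and the treatment term tends to survive when the chance baseline gap is large, which is when adjustment matters most. That is not a pre-specified adjustment. Nor is this merely detail left out of a condensed article: the article writes out the fixed part and its selection rule, and the weakness lies in what it writes.

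**Conclusion.** The point holds as a matter of efficiency and pre-specification. It does not show bias, or a trial that misses its stated power.

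For the change contrast that reproduces the planned size, the loss is modest: 12.5% of variance with equal SDs and about 4% with the Table 1 SDs at r = 0.75, growing to about 11% and 16% with the Table 1 SDs at r = 0.6 and 0.5. The loss is large, power about 0.52 against 0.86, only for an unadjusted difference at a visit. The article does not rule that contrast out, because it names no primary contrast.

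These figures assume 33 analysed per arm, a 7.5-point difference, a two-sided 5% test and a single follow-up visit. The powers of 0.52, 0.81 and 0.86 also assume an SD of 15 at both visits and r = 0.75. The amendment is worth making because it costs almost nothing and settles the treatment of baseline before results are seen.

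**What to change.** In Statistical analysis, for each of the two parts, state one of the following:

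- Baseline POSAS is kept as a response, the arms share a common baseline mean, and treatment effects enter only at post-treatment visits.
- Post-treatment POSAS is the response, and baseline POSAS is a fixed covariate.

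State that these terms and the treatment effect are exempt from Wald elimination, and name the contrast that is the primary treatment effect. Handle Skindex-29, SF-36 and keloid volume in the same way, each with its own baseline.

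The cost is one or two sentences, with no new data and no extra patients. The covariate version needs a simple rule for patients without a baseline score; the common-baseline version does not.

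### The primary POSAS model lets significance tests delete its own treatment terms, so the 0.05 type I error is not assured and the reported treatment effect depends on the data

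*Protocol article*

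**What the plan says.** The Statistical analysis section of the protocol article describes the starting fixed part thus: "We take in account time, logarithm of time and squared time, treatment condition and its interactions with time". The next step is: "Nonsignificant effects will be excluded using Wald tests". Nothing sets the treatment terms apart from the time terms in this step. The random part, a possible third level and the patient-level covariates are also chosen by fit or significance. The final fixed model is then compared with the saturated one by ordinary maximum likelihood. Treatment differences are to be given as effect sizes, standard errors and P values; the natural reading is that these come from the final model.

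The Data collection section gives the visits: "Data are collected at baseline, before randomisation, and at follow-up assessments 2, 12, 26, and 52 weeks after treatment". The Sample size calculation section sets the error rates: "Type 1 error (alpha) was set at 0.05, and power (1-beta) on 0.80".

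**The concern.** Backward elimination is a tolerable way to find a simple time curve. It becomes a problem when the terms searched over include the treatment effect that the trial exists to test. Three things follow.

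- The form of the treatment effect is decided by the data. The final model may hold a treatment main effect, an interaction with linear, log or squared time, or a mixture.
- The standard errors and P values of the final model treat that form as if it had been fixed beforehand, although its terms were kept because they were significant.
- The 0.05 in the sample size section belongs to a single planned test. It does not carry over to what survives a search over up to four treatment terms (one main effect and three interactions).

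The trial has two parts, each with its own primary comparison, and neither patients nor physicians are blinded. A primary analysis that leaves no choices open until the data are seen is worth more than usual here.

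**Working it through.** **1. Reproduce the plan's own figure.** Inputs from the Sample size calculation section: "The assumed medium-sized effect of 0.5, based on a SD of around 15 (Table 1), corresponds to 7.5 points on the POSAS scale"; "We assumed a correlation of 0.75 between time points"; alpha 0.05 (taken as two-sided) and power 0.80.

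- SD of a change score: 15 × √(2 × (1 − 0.75)) = 10.6.
- n per group = 2 × (1.960 + 0.842)² × 10.6² / 7.5² = 2 × 7.85 × 112.5 / 56.25 = 31.4, so 32. The noncentral-t version gives 33 (power 0.808).
- Loss to follow-up: 33 / 0.75 = 44; 44 × 4 = 176.

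This matches the stated 33 per group and "this results in a total sample of 176 subjects". The stated size is thus what one fixed change-score comparison needs. It is not derived from the elimination procedure.

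**2. Null error of the elimination rule.** 20,000 simulated trials per row, 33 per arm, visits at weeks 0, 2, 12, 26 and 52, no treatment effect, complete data, covariance treated as known. Starting terms: time, log(time + 1), time squared, treatment and its three interactions. Backward deletion by Wald tests at an assumed two-sided 0.05. Covariance is either compound symmetry (SD 15, correlation 0.75) or an assumed random intercept and slope. In a hierarchical search, a lower-order term stays while its interaction stays.

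| Covariance | Search | Arms at baseline | Any treatment term survives | Week-52 difference from selected model significant |
|---|---|---|---|---|
| Compound symmetry | free | free | 24.6% | 12.3% |
| Compound symmetry | free | set equal | 20.4% | 8.1% |
| Compound symmetry | hierarchical | free | 18.2% | 5.5% |
| Compound symmetry | hierarchical | set equal | 13.9% | 7.2% |
| Random slope | free | free | 24.0% | 11.7% |
| Random slope | free | set equal | 20.4% | 8.3% |
| Random slope | hierarchical | free | 18.2% | 6.0% |
| Random slope | hierarchical | set equal | 13.6% | 7.3% |

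Monte Carlo standard error near 5% is √(0.05 × 0.95 / 20,000) = 0.15 percentage points. A separate run of 4,000 trials put the week-52 error at about 6% with hierarchy and 13% without. As a reference, four independent tests at 0.05 give 1 − 0.95⁴ = 18.5%, and three give 14.3%.

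**3. The same data without elimination.** One week-52 treatment contrast from the full model: 4.9-5.3%. One joint Wald test of all treatment terms: 4.8-5.2%.

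**4. Dependence on baseline handling.** With weeks 2 to 52 only and plain log(time), a treatment term survives in 17% (hierarchical) or 24% (free) of null trials. The result does not turn on how baseline or log time is coded.

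**5. Under a true effect.** With a constant 7.5-point benefit after baseline and a hierarchical search, the selected treatment part was the log-time interaction alone in 34% of trials, all three interactions in 29%, linear plus log in 23%, nothing in 5% and the main effect alone in 4%. The SD of the selected week-52 estimate was about 2.9-4.1 points. A fixed baseline-adjusted week-52 contrast under compound symmetry has 15 × √(1 − 0.75²) × √(2/33) = 2.4. Not all of that gap comes from selection: a fixed week-52 difference without baseline adjustment has 15 × √(2/33) = 3.7.

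**The case against.** The strongest reply is that the size of the inflation rests on a decision rule the article does not state. The 14-25% range counts a trial as positive when any treatment term survives. If the investigators meant to read a week-52 difference from a hierarchical model, the error is 5.5-7.3%, which is mild. This stands, and it is why the size is given as a range by reading and not as one figure.

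It can also be said that naming the primary visit or contrast is commonly left to an analysis plan, which is not shown. That stands too, and the missing visit is not the point here. The elimination rule, however, is written into the article, and a later plan would have to overturn it.

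The article does include a check of the final model against the saturated one. That check concerns fit. It does not adjust the inference for the search.

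A reader might infer more than the text supports:

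- That baseline is averaged into a diluted main effect. That needs the main effect alone to survive, which happened in fewer than 5% of simulated trials with a true benefit.
- That log time at week 0 is an error. An offset or other coding of time is detail that a condensed article may omit.
- That week-2 scores are taken on unhealed skin. The article ties complete healing only to the volume mould.
- That the result cannot be set against the six-point criterion. Any selected model still yields a difference in POSAS points at each visit.

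**Conclusion.** The point holds in this form: the article states a rule that lets significance tests remove the treatment terms under test. The reported effect then depends on the data, its standard error ignores the selection, and the 0.05 type I error is not assured.

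The null error is about 5-7% (week-52 difference, hierarchical selection), about 8-13% (the same without hierarchy) or about 14-25% (any surviving treatment term), against about 5% for one prespecified test in a fixed model. It would be tempting to conclude that the trial runs a false-positive rate near 25%, or that its primary effect is undefined. The documents support neither: they do not say which reading applies, and an analysis plan may name a contrast.

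The figures assume a two-sided 0.05 Wald threshold, log(time + 1) where baseline is included, complete data, known covariance and 1:1 allocation. The further selection of random effects, third level and covariates was not simulated.

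**What to change.** For each of the two parts:

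- Keep treatment and all treatment-by-time terms in the primary model, exempt from elimination.
- Name one primary treatment test and report it with a 95% confidence interval. One option is the baseline-adjusted difference in POSAS total at week 52, in line with the one-year rationale under Trial design. Another is a single joint test of all treatment terms, which should be accompanied by a named difference in points.
- Fix baseline POSAS and the three minimisation factors (skin type, location, duration) as covariates in advance.
- Keep the selected time-curve models as exploratory.

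Categorical visits and an unstructured covariance are one sound way to do this, not the only one.

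The cost is a change of wording before data lock and the loss of the flexible curve as the primary result. No patients, visits or data are added. The total of 176 stands for a fixed change-score comparison. For a baseline-adjusted comparison under the plan's own SD and correlation, 29 per group suffice and 33 give power 0.856.

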## Methods/Design

### Trial design

The design is a multicentre, randomised controlled open trial, which used minimisation to control for skin type, location and duration of disease. The trial consists of two parts: one for primary keloids and one for resistant keloids. Primary keloids are keloids that have not been surgically treated and, to some extent, have responded to corticosteroids. Resistant keloids are keloids that recurred after excision or those that did not respond to corticosteroids (progression within six weeks after corticosteroid injection).

For the primary keloids we randomise between either intralesional cryotherapy or excision and additional corticosteroids. The resistant keloids are randomised between either intralesional cryotherapy or excision and brachytherapy. Follow-up assessments are in weeks 2, 12, 26, and 52 post-treatment. The follow-up period is based on scar maturation, which lasts about one year, and the chance of recurrence that usually occurs within the first year [22,23].

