### Patient recruitment

Patients who present with a keloid at an outpatient clinic of the four participating centres are considered for the study. A keloid is a clinical diagnosis and is distinguished from hypertrophic scars by the clinician’s judgement. The judgement between hypertrophic scars and keloid is based on: the growth history, starting early versus late after trauma, remaining stable versus still growing; shape, following initial lesion versus not following the initial lesion; and size, <0.5 cm versus >0.5 cm beyond the original lesion.

At a later stage, we will report how many patients with keloids were seen and how many were eligible for the study. Inclusion criteria are:

1. Keloid with a surgical indication.

2. One to three keloids that can be treated in one session.

3. Minimal size of 1 × 1 cm.

4. Suitable for excision and primary closure.

5. Patient aged between 18 and 75 years.

6. Fully mentally competent.

7. Sufficient knowledge of the Dutch or English language.

Exclusion criteria are:

1. Hypertrophic scars.

2. Scars after burn wounds.

3. Keloids less than one year old.

4. Pregnancy.

5. Use of systemic chemotherapeutics or chronic use of systemic corticosteroids or immunosuppressive medication.

6. Hypersensitivity for local anaesthetics, adrenaline, or triamcinolone (primary keloids).

7. Patients not sufficiently fit for brachytherapy (resistant keloids).

8. Severe comorbidity with life expectancy under one year.

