### Randomisation (treatment allocation)

Previous studies on keloid treatment showed that specific characteristics are predictors of recurrence. Therefore, we want to assure homogeneity between treatment groups regarding these characteristics, such as duration of the keloid existence (dichotomous; <5 years or ≥5 years) and location of the keloid (categorical; sternal region, auricular region and other). In addition, we try to match for skin type because of the strong association with the development of keloids, but the doubtful relation with recurrence rate (categorical; Fitzpatrick type 1 and 2, type 3 and 4, type 5 and 6). Because of the many different strata that would be formed and considering the total number of patients to be included, we choose not to use permuted blocks but will use the more sophisticated technique of minimisation. We will minimise on the three factors previously mentioned. The allocation of a new subject is determined by the allocation of the subjects already enrolled. We apply a 20% random chance factor to keep allocation predictability at a minimum. The software used is the open source program MinimPy (http://minimpy.sourceforge.net/).

When a patient agrees to participate in the study they irrevocably receive a unique identification number, which cannot be changed or removed from the database. After completion of baseline measurements, treatment allocation is conducted through a central computerized allocation using the locked database for all participating centres. Then the physician and the patient are informed of the assigned condition and the treatment is planned. In this way, allocation concealment is guaranteed.

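### The three factors used to minimise allocation stay in the model only if significant or if fit improves; they should be fixed covariates set in advance

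*Protocol article*

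**What the plan says.** Under Trial design, the protocol article says that the trial "used minimisation to control for skin type, location and duration of disease". The Randomisation section confirms it: "We will minimise on the three factors previously mentioned". Duration has two categories, location three, and skin type three ("Fitzpatrick type 1 and 2, type 3 and 4, type 5 and 6"). The stated reason is that such characteristics predict recurrence, although for skin type that relation is called doubtful.

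The Statistical analysis section gives the same factors two conditional roles:

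- As a grouping level: "If necessary, a third level of subgroups with specific characteristics (skin type, duration of keloid disease and location of the keloid) can be added". It is kept if it improves model fit.
- As covariates: "When characteristics like sex, age, skin type, duration of keloid disease and location of the keloid make a significant contribution to the model", they are taken into the model. Here they are listed with sex and age, which were not used in allocation. In the fixed part, nonsignificant effects are removed by Wald tests.

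No sentence says that the minimisation factors are always adjusted for.

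**The concern.** Minimisation makes the arms more alike on the chosen factors than simple randomisation would. If these factors predict the outcome and the analysis leaves them out, the model puts their variance in the error term although the allocation has already removed most of it from the treatment comparison. The reported standard error is then too large and power is lost.

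Selecting them by significance brings a different problem. The covariate set depends on the data. It can differ between the two trial parts and between outcomes, and the final P value takes no account of the selection. In an open trial it is better that nobody has this choice once data are in.

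The third level does not solve this. A random level suits a sample of many units. Each of these factors has two or three categories, too few to estimate a variance. The article also does not say how a factor can serve both as a level and as a covariate.

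**Working it through.** **1. The plan's own sample size.** Inputs from Sample size calculation: SD 15, difference 7.5, correlation 0.75, alpha 0.05 (taken as two-sided), power 0.80, 25% loss, four groups.

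- SD of a change score = 15 × √(2 × (1 − 0.75)) = 10.61.
- Patients per group for a difference of 7.5: 32 by the normal approximation, 33 by the noncentral t.
- 33 / 0.75 = 44; 44 × 4 = 176.

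The stated 33 and 176 reproduce. Each trial part has 2 × 44 = 88 randomised and 2 × 33 = 66 evaluable patients.

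**2. Upper bound for full omission.** With perfect balance, true SE / reported SE = √(1 − R²), where R² is the share of outcome variance explained by the three factors.

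- R² = 0.10: 1/√0.90 = 1.054, so the SE is 5% too large; critical value 1.96/0.949 = 2.066, actual two-sided level 0.039.
- R² = 0.20: 1/√0.80 = 1.118, so the SE is 12% too large; critical value 2.191, actual level 0.028.

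This design does not reach perfect balance. Allocation has a random element ("We apply a 20% random chance factor to keep allocation predictability at a minimum"), and a quarter of patients may be lost.

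**3. Simulation of one trial part.** 88 patients were minimised on factors with 2, 3 and 3 levels, with 25% lost at random and 4000 runs per setting. The preferred arm was assigned with probability 0.8 or 0.9, two readings of the 20% random element. The outcome was a change score with SD 10.61.

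Assumptions not in the article: R² from 0 to 0.3, shared equally by the factors; level frequencies of 50/50, 25/35/40 and 25/30/45%; elimination at P > 0.05; one change score in place of the full mixed model. Ranges cover the two allocation probabilities.

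| R² | Analysis | Model SE / true SE | Type I error | Power at 7.5 points |
|---|---|---|---|---|
| 0.1 | none of the factors | 1.025 | 0.044-0.047 | 0.80-0.81 |
| 0.1 | kept if significant | 0.979-0.981 | 0.052-0.056 | 0.82-0.83 |
| 0.1 | all three fixed | 0.986-0.991 | 0.045-0.054 | 0.82-0.83 |
| 0.2 | none of the factors | 1.061-1.079 | 0.034-0.037 | 0.82 |
| 0.2 | kept if significant | 0.983-0.989 | 0.051-0.052 | 0.86 |
| 0.2 | all three fixed | 0.990-0.996 | 0.047-0.051 | 0.87 |
| 0.3 | none of the factors | 1.115-1.117 | 0.025-0.030 | 0.82-0.83 |
| 0.3 | kept if significant | 0.987-0.989 | 0.054-0.055 | 0.90-0.91 |
| 0.3 | all three fixed | 0.996 | 0.051-0.053 | 0.91 |

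At R² = 0, fixing all three factors gave power of 0.79-0.80, against 0.81 without them.

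Simulation error is about √(0.05 × 0.95 / 4000) = 0.003 for the type I error and about 1/√(2 × 4000) = 1.1% for the SE ratio. The distortion under the significance rule is therefore close to what the simulation can resolve.

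**4. How unstable the selected model is.** With all three factors truly prognostic, the significance rule kept on average 0.8 of the 3 at R² = 0.1, 1.6 at 0.2 and 2.3 at 0.3.

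**5. The third level.** Taken singly, each factor offers 2 or 3 units. If the factors were crossed, which the article does not say, there would be 3 × 3 × 2 = 18 cells, with 88/18 = 4.9 randomised or 66/18 = 3.7 evaluable patients each.

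**The case against.** The best defence is that the plan does not discard the factors. It keeps those that matter, and strongly prognostic factors usually pass the test. The simulation supports this: under the stated rule the SE is slightly too small rather than too large, and almost no power is lost against full adjustment. This part of the defence stands.

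A second objection is also sound. The model contains treatment-by-time terms, and baseline is one of the measurement times. A factor that shifts a patient's score equally at every visit cancels from a change contrast, so leaving it out does no harm there. Harm from omission requires that the factor predict the contrast being analysed, and the article gives no figure for that.

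A reader might also infer that centre must be in the model for the same reason, given that "Patients who present with a keloid at an outpatient clinic of the four participating centres are considered for the study". That does not follow. Centre was not a minimisation factor, so leaving it out does not disregard the allocation. The Outcomes section names a clinician and an investigator as observers but does not say that they are specific to a centre. Adjusting for centre is a reasonable separate choice.

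None of this defends choosing the covariates from the data when the allocation has already singled out three of them.

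**Conclusion.** The point holds as one of prespecification. The plan states a rule, so this is not a detail left for the analysis plan, and the rule allows the primary model to omit allocation factors according to what the data show.

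The expected distortion under that rule is small: SE about 1-2% too small, type I error up to about 0.056. Complete omission is the worse case. Its SE excess of about 2.5%, 6-8% and 11-12% at R² of 0.1, 0.2 and 0.3 rests on assumed R² values and on the factors predicting the analysed contrast. It errs on the conservative side. At R² = 0.3 power is 0.82-0.83 instead of 0.91.

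A reader might go further and conclude that the trial's standard errors will be 5-12% too large, with a true test level of 3.9-2.8%. The article does not support that. Those figures need all three factors dropped after perfect balance. The stated rule does not drop all three as a matter of course, and the allocation method does not give perfect balance.

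**What to change.** In the primary POSAS mixed model and the models for the other continuous outcomes, include skin type (3 categories), location (3) and duration (2) as fixed effects whatever their P values. Exempt them from the Wald elimination and delete the third-level option. State whether they enter as main effects only or also with time, since a main effect alone does not adjust a change contrast.

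Choose any other covariates, such as sex, age or centre, in advance and not by significance. Do not force the full set into time to recurrence or complication rates, where events may be few.

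Cost: a change of wording, using data already collected for allocation. Main effects take 2 + 2 + 1 = 5 degrees of freedom per trial part; terms with time would take more. The sample size of 176 stays as it is.
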